### Sample Size and Randomization

Assuming that the prevalence of obesity varies across schools according to a log-normal distribution with a mean value of 3% and a SD of 2%, 125 children per school in each of the 8 schools would provide a prevalence estimate between 1.5% and 5% with a probability of 95%. Under this assumption, 95% of school-specific prevalence would range between 0.8% and 8.2%. Hence, our aim is to recruit 125 children per school.

The power calculation for the intervention study is based on the change in a quantitative outcome variable from baseline to follow-up. We denote the SD of its change across schools and children by sigma (σ). Assuming an intervention effect size of 0.5 x σ and an intraclass correlation of .04 for the clustering of individual changes within schools (corresponding to a random effect SD of 0.2 x σ), 400 children in the 4 intervention schools (ie, 100 children per school) participating in baseline and follow-up, and 400 children in the 4 control schools would provide over 85% power to observe a statistically significant difference in the mean change of the respective outcome variable between intervention and control schools at the 5% level.

Enrollment of schools will be done by the local research team. To prevent contamination of the intervention effects, schools rather than classes were randomized in January 2019. Before randomization, schools were divided into 2 geographic groups; namely, township areas and northern areas, each containing 4 schools. Township areas are predominantly inhabited by black Africans and northern areas by colored people (after an apartheid-era classification, which refers to people from a multiracial ethnic background and can include persons of Khoi and San origin).

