The randomization into intervention and control schools was done separately in each of the 2 groups so that each group was assigned 2 intervention and 2 control schools. To keep the design as balanced as possible, the 4 intervention schemes (ie, teaching materials only, teaching materials plus teacher workshops, teaching materials plus teacher coaching, and teaching materials plus teacher workshops plus teacher coaching) will be assigned in such a way that the intervention schools of 1 group will get teaching materials plus either teacher workshops or teacher coaching. Randomization will allow to determine which of the 2 groups gets which of the 2 pairs of intervention schemes. Sequentially numbered, opaque, sealed envelopes will be used for the assignment of the intervention arms to the schools.

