#### Data Collection and Statistical Analysis

The following data will be collected: (1) quantitative data on blood pressure, glycated hemoglobin and blood lipids, anthropometry and levels of physical fitness, cognitive performance and psychosocial health, (2) SES and demographic data, and (3) qualitative data on the feasibility and acceptability of the intervention measures implemented through FGDs. Quantitative data will be entered twice and cross-checked using EpiData version 3.1 (EpiData Association; Odense, Denmark). Cleaned data will be transferred to STATA version 13.0 (STATA Corp, College Station, TX, United States of America). Questionnaire data will be collected using the software package EvaSys (Survey Automation Suite, version 7.1) and analyzed with STATA.

Clinical and anthropometric indicators, physical fitness, cognitive performance, and psychosocial health values will be summarized by their mean and SD at normal distribution and otherwise by their median and interquartile ranges. Questionnaire information on psychosocial health will be expressed as a percentage.

For the analysis of cross-sectional and longitudinal associations, mixed linear or mixed logistic regression models will be used, depending on the type of outcome variable. These models will be adjusted for clustering within classes and schools using random intercepts. In analyses of cross-sectional associations, the models will include personal characteristics of children, such as gender and age, SES of parents or guardians, and other potential confounders of the associations of interest. Models assessing intervention effects will additionally include 3 indicator variables, as defined at the level of schools, 1 for schools of the intervention arm, 1 for schools receiving teacher workshops, and 1 for schools receiving teacher coaching. In addition, these models may include the value of the respective outcome variable at baseline. As intervention effects may also depend on the child’s initial characteristics, stratified analyses and analyses with interaction terms will be performed. Potential effect modifiers to be tested include gender, age, SES, ethnicity, health status, and physical fitness at baseline.

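### Schools were randomised within two geographic areas, but the intervention model names no area term, and area-by-intervention is aliased with workshop-by-coaching

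*Protocol article*

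**What the plan says.** Under Sample Size and Randomization, the article states: "Before randomization, schools were divided into 2 geographic groups; namely, township areas and northern areas, each containing 4 schools". It describes the two groups as predominantly black African and predominantly colored communities. It continues: "The randomization into intervention and control schools was done separately in each of the 2 groups", with two intervention and two control schools in each.

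The four component schemes are then tied to area: "the intervention schools of 1 group will get teaching materials plus either teacher workshops or teacher coaching". By elimination, the intervention schools of the other area receive materials only and materials plus both components. Chance decides only which area gets which pair.

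Under Data Collection and Statistical Analysis, the models carry random intercepts for class and school. Models for intervention effects add three school-level indicators: "1 for schools of the intervention arm, 1 for schools receiving teacher workshops, and 1 for schools receiving teacher coaching". The baseline outcome may also enter. Geographic area is not named. Ethnicity appears in the list of modifiers: "Potential effect modifiers to be tested include gender, age, SES, ethnicity, health status, and physical fitness at baseline".

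Under Study Design, the primary comparison is all four intervention schools against all four control schools. The article argues there that analysing change makes pre-existing differences between schools matter less.

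**The concern.** The investigators thought area important enough to randomise within it, but the described analysis does not use it. Analysing change removes a difference in level between areas, not a difference in how much children change. If township and northern schools change by different amounts over the 36 weeks, that difference counts as unexplained school-to-school variation, although the design has balanced it out. With eight schools, little power can be spared.

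The second issue is interpretation. Because each area holds a fixed pair of schemes, a different intervention effect in the two areas looks exactly like an interaction between workshops and coaching. A reported modification by ethnicity, which largely follows area, could be synergy or antagonism between the two components, or the reverse.

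**Working it through.** **Inputs** (Sample Size and Randomization): effect 0.5 σ; ICC .04 (school SD 0.2 σ); 100 children per school; 4 against 4 schools; 5% level, taken as two-sided.

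**Reproducing the plan's figure.** Design effect = 1 + 99 × 0.04 = 4.96. Effective n per arm = 400 / 4.96 = 80.6. Two-sided power on a normal reference = 88.8%, which agrees with the claim that the sample "would provide over 85% power to observe a statistically significant difference in the mean change of the respective outcome variable". With a t reference on 6 between-school df it is 75.4%.

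**Layout of school means.** Variance of a school mean = 0.04 + 0.96/100 = 0.0496 σ². Area is orthogonal to arm, workshop and coaching, so adding it leaves the variance factor of the arm coefficient unchanged and its omission causes no bias.

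- Arm only: factor 0.5, SE = √(0.5 × 0.0496) = 0.157 σ; 6 df, or 5 with area.
- Arm, workshop, coaching: factor 1.0, SE = √0.0496 = 0.223 σ; 4 df, or 3 with area.

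**Effect of omitting area.** Let d be the area difference in mean change. It adds 8 × (d/2)² = 2d² to the residual sum of squares. The expected residual variance becomes 0.0496 + 2d²/6 (arm only) or 0.0496 + 2d²/4 (three indicators). At d = 0.2 the SE rises by √(0.0629/0.0496) − 1 = 13% and √(0.0696/0.0496) − 1 = 18%; at d = 0.3, by 27% and 38%.

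**Power for 0.5 σ** (simulation of eight school means, 200,000 trials per cell, t reference, ICC .04 taken as within area; d is an assumption):

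| d (σ) | Arm only, no area | Arm only + area | Three indicators, no area | Three indicators + area |
|---|---|---|---|---|
| 0 | 75% | 72% | 40% | 35% |
| 0.1 | 73% | 72% | 37% | 35% |
| 0.2 | 66% | 72% | 29% | 35% |
| 0.3 | 56% | 72% | 18% | 34% |

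The columns cross at about d = 0.12 to 0.15 σ. The three-indicator columns are for the arm term, which in that model is the effect of materials alone. Their lower level comes from that model's larger variance and fewer df, not from area.

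**If the ICC of .04 already includes area**, the within-area school variance is 0.04 − d²/4. Arm-only power without area then stays at 74 to 75% up to d = 0.3; with area it is 81% at d = 0.2 and 93% at d = 0.3. In the three-indicator model, power without area is 33% at d = 0.2 and 21% at d = 0.3, against 41% and 54% with area.

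**Reference distribution.** With no area difference, using 1.96 instead of the t quantile gives type I error P(|t| > 1.96): 9.8% on 6 df, 10.7% on 5, 12.2% on 4 and 14.5% on 3.

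**Alias.** Let I, W and C be the arm, workshop and coaching indicators, and A = 1 in the area with the workshop-only and coaching-only schools. In all eight schools W·C = ½(W + C − A·I):

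- workshop only or coaching only: ½(1 − 1) = 0
- both: ½(2 − 0) = 1
- materials only and controls: 0

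The design matrix with intercept, I, W, C, A, A·I and W·C accordingly has rank 6 of 7. More children from these schools would not change that.

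**The case against.** The strongest reply is that the covariate list is not closed. The article says the three indicators are included additionally, just after mentioning gender, age, socioeconomic status and other potential confounders, and a fuller analysis plan may exist. It is fair that the text does not exclude area. But that sentence concerns cross-sectional associations and names no area term, while the school-level terms for intervention effects are listed without the randomisation factor.

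Second, the loss depends on an area difference in change that the documents never give, and the stated ICC is not qualified as within area. This stands. It makes the size conditional, and for a small difference the area term lowers power.

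Third, a reader might infer that the model as described is simply conservative. That holds only with a small-sample t reference, which the article does not state; its own power figure reproduces on a normal reference. With a normal reference, the three-indicator model is anti-conservative when areas do not differ (about 12%), and adding area alone would make that worse (about 14%).

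Fourth, a reader might infer that ethnicity is fully aliased. The article says only that each area is predominantly of one group, and it treats ethnicity as a characteristic of the child. The alias is exact for area and approximate for ethnicity; within-school variation in ethnicity carries some information.

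**Conclusion.** The point holds as a matter of efficiency and interpretation. The described model omits the factor within which schools were randomised. With a t reference and an ICC that excludes area, an assumed area difference of 0.2 to 0.3 σ costs roughly 5 to 16 points of power in either model compared with including area. At 0.1 σ or below, including area costs a little instead. If the ICC already includes area, arm-only power does not fall noticeably below its 75% t-based level, and the omission is a gain not taken.

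One might be tempted to say the omission biases the effect or invalidates the trial. It does neither, because area is balanced against arm, workshop and coaching.

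The alias needs no assumed value. Area-by-intervention and workshop-by-coaching are the same contrast in this design, and a test of ethnicity as a modifier largely inherits the problem. The article gives no warning of this.

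**What to change.** Add a fixed effect for area (township or northern) to every model of intervention effects, and base tests and intervals on a small-sample reference with between-school degrees of freedom. The two changes belong together: with a normal reference, adding area would give type I error of about 11% (arm only) to 14% (three indicators).

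State that the workshop and coaching main effects assume no interaction between them. State also that modification by area cannot be separated from a workshop-by-coaching interaction, and modification by ethnicity can be separated only through within-school variation in ethnicity, so neither supports a firm conclusion.

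The cost is one of 6 between-school df (arm only) or one of 4 (three indicators). If the areas do not differ, that is about 3 to 4 points or 6 points of power; there is a net gain above roughly 0.12 to 0.15 σ. The rest is a few lines of wording, with no change to design or data collection.

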### Availability of Data and Materials

The datasets generated and/or analyzed during the present study are not publicly available due to confidentiality but are available from the corresponding author on reasonable request.

## Results

### Overview

The project was funded in April 2017 and enrollment of the participants was completed in January 2019. The baseline survey was conducted from January to March 2019. At the time the present paper is being written, the *KaziKidz* and *KaziHealth* intervention are underway. The follow-up survey is planned for September to October 2019. At the end of the study, the results will be communicated to the Department of Health and the Department of Education in Port Elizabeth, as well as the involved schools. All intervention materials will be made available to the control schools after completion of the study. Workshops will be offered to the control schools to prepare teachers to implement the *KaziKidz* teaching material. Furthermore, teachers of the control schools will have the possibility to take part in the workplace health promotion intervention program after the completion of the second health assessment. The key findings will be submitted for publication to the peer-reviewed literature and presented at national and international conferences.

## Discussion

### Principal Findings

Results from the DASH study revealed that the prevalence of soil-transmitted helminth infections among grade 4 children was above 60% (90/149) in several schools in Port Elizabeth [56]. Moreover, infected children had lower VO_2_ max compared with their noninfected peers [56]; helminth infections and low physical fitness were significant predictors of low selective attention and poor academic achievement [16]; physical activity was associated with health-related quality of life [57]; almost one-third of all school children were classified as hypertensive [58]; and the physical activity intervention component contributed to the maintenance of academic performance [27] and resulted in a significantly delayed increase in children’s BMI [59]. Importantly, the DASH intervention package was well received in all schools.

The *KaziBantu* project is a logical continuation and expansion of the DASH project and aims at contributing to healthy schools and healthy communities. Teachers, as leaders in communities, have an important role to play in this regard. We conjecture that teachers as healthy role models will be able to promote better health behaviors and encourage a healthy, active, and inspiring environment for learners and peers at school. Various health professionals will empower teachers with specific knowledge related to infectious and NCD risk factors, physical activity and fitness, and psychosocial health and nutrition. Improved health and well-being increase teachers’ productivity, benefiting their own health and well-being and that of the children they teach and educate. We hypothesize that implementing *KaziBantu* will result in less absenteeism, a reduction in stress, and better coping with work demands.

Pursuing the present study protocol will provide specific answers to the following questions: Are *KaziKidz* teaching materials useful? What are the difficulties in using the teaching materials from the perspective of the teachers? What are the teachers' experiences with regard to the coaching by the teacher coaches? What experiences do the coaches have in their work with the teachers? What attitudes do teachers have with regard to the lessons proposed? What are the conditions for an effective and sustainable implementation of this teaching material? Does the acceptance of the *KaziKidz* teaching material by the teachers moderate its effectiveness?

With regard to the implementation of *KaziKidz* and *KaziHealth*, 3 languages are spoken by the communities in the study area, namely, Afrikaans, IsiXhosa, and English. To ensure comprehension, questionnaires translated into the local languages have been pretested by native speakers, with an emphasis on those that focus on mental health indicators to match the educational attainment of children and help them to understand and answer the questions. The study will be conducted in impoverished and harsh environments where illiteracy, neglect, and violence are common [60,61], which might have an impact on the granting of informed consent by parents and guardians. For illiterate parents or guardians, a literate witness will be invited to sign, whereas participants will be asked to provide a thumbprint. To ensure return of the signed consent forms, we might ask potential study participants several times. Specific safety measures are in place to implement the research. Although it is difficult to predict the extent of people’s mobility and movement, we anticipate a substantial loss to follow-up as people show considerable mobility in this setting. Multiple imputations will be used to deal with missing data, as appropriate.

### Conclusions

Taken together, the *KaziBantu* project presented here builds upon the previous DASH study and aims to improve physical health and well-being, cognitive performance, and psychosocial and clinical health of children and teachers. The South African Department of Education seeks to create a lifelong learner who is confident, independent, literate, numerate, multiskilled, compassionate, and has respect for the environment and the ability to participate in society as an active citizen. The Department of Education also envisions healthy teachers who are qualified, competent, dedicated, and caring and who will be able to fulfill the various roles of an educator. Hence, the project aspires to assist the Department of Education by contributing to the development of the full potential of each learner and the transformation of education in South Africa. In addition, developed and validated *KaziKidz* workshop material may be translated into short learning programs for accreditation of Teachers’ Continued Professional Development. The *KaziChat* app will be made available to the Department of Education's directorate responsible for human resources for distribution to all teachers together with encouragement for implementation. This study builds on local evidence and offers the opportunity of providing new evidence on health intervention responses to NCD risk factors as a benchmark for future controlled studies that will enable comparisons among marginalized communities between South Africa and other African countries.

## Abbreviations

BMI: body mass index
CDC: Centers for Disease Control and Prevention
DASH: Disease, Activity and Schoolchildren’s Health
DXA: dual-energy x-ray absorptiometry
EKNZ: Ethics Committee Northwest and Central Switzerland
FGD: focus group discussion
HDL-C: high-density lipoprotein cholesterol
LDL-C: low-density lipoprotein cholesterol
LMIC: low- and middle-income country
MVPA: moderate-to-vigorous physical activity
NCD: noncommunicable disease
non-HDL: nonhigh density lipoprotein cholesterol
NTD: neglected tropical disease
PE: physical education
POC: point-of-care
RCT: randomized controlled trial
SES: socioeconomic status
VO_2_max: maximal oxygen uptake
WHO: World Health Organization
